##### Stimuli

Facial pictures are grayscale photographs selected from the native Chinese Facial Affective Picture System [16], and a total of 60 facial pictures are used as target faces (20 happy, 20 neutral, and 20 fear faces) with an equal number of males and females. Each picture was assessed for its valence and arousal on a 9-point scale with a large sample of Chinese participants in a previous survey. Each pair of facial stimuli will consist of a neutral picture and an emotional picture. Thus, we will have pairs of emotional-face stimuli consisting of 60 emotional faces, including 20 happy-neutral, 20 sad-neutral, and 20 fear-neutral pairs of facial stimuli.

##### Procedure

The experimental paradigm is a modified dot-probe paradigm. The task consists of 160 trials. A central fixation appears for 300 ms, and then replaced by a pair of emotional-face stimuli with different valences as a cue, which will last for 500 ms. After a short 200-ms interval, the dot probe is randomly presented for 150 ms as a target in either the left or right position of the fixation cross. The participant is asked to identify the spatial location of the “dot” and register the response with the forefinger pressing the button “1” or “4” on the reaction box as quickly as possible. An automatic interval of 2000 ms is programmed to receive the participants’ response; after a response is made or 2000 ms (whichever occurs first), a black screen is presented for 600 ms and followed by the subsequent trial [25].

##### ERP data

During the cognitive task, ERP data will be recorded by the NeuroScan ERP system (NeuroScan Company, American), which contains a 64-channel amplifier and a 64-electrode Ag/AgCL scalp cap. Each epoch following the emotional-face cue and target will mainly be analyzed by an off-line analysis using MATLAB 2013a (The Mathworks, Natick, USA) as well as its toolbox ERPLAB toolbox (http://www.erpinfo.org/erplab). The latency and average amplitudes of the three ERP components P100, N170, and P300 will be recorded and have been detected in various stages of attention processing.

##### Behavioral data

E-Prime software (Psychology Software Tools Inc.) will be applied to program the experimental procedure, record the accuracy of the responses, and the behavioral reaction times (RT) together with the ERP data.

### Safety evaluation

Adverse events (AEs) during the treatment will be recorded. AEs include the following: hematoma around the site of needling insertion points, local numbness, pain, and dizziness during treatment. If any AE occurs, the doctor will assess and provide corresponding treatment to the patient in accordance with the study protocol, and report the adverse events form in the case report form.

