Studies have shown that depression is associated with cognitive control deficits with regard to emotional information [14]. MDD is characterized by abnormal cognitive processing of negative bias, which is manifested by paying excessive attention to negative emotional information [15, 16]. The cognitive processing bias of negative emotions penetrates the whole process of depression and is at the core of the development of depressive symptoms. It is very important to understand the effects of acupuncture on cognition as it relates to PSD because understanding the relationship between emotions and cognitive function can help to explain the antidepressant effects. Event-related potentials (ERPs) reflect neural activities in the cognitive process, and because their assessment is noninvasive and has high time resolution (milliseconds), ERP measurements have become the preferred technology for studying neurocognition. According to a recent study, the recurrence and severity of depression may disrupt emotional processing, and the ERP component may be a potential biomarker to predict depression and cognitive function [17]. Thus, ERP can be adopted to explore the effect of acupuncture treatment on the negative emotion processing bias in PSD.

This randomized, placebo-controlled, single-blinded study was designed to explore the efficacy and safety of acupuncture on PSD and to explore its effect on cognitive function. It is hypothesized that acupuncture treatment will improve symptoms of depression, cognitive function, and abnormal negative emotion processing bias in individuals with PSD.

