### Intervention

The enrolled PSD participants receive basic treatment for stroke: basic pharmacotherapy treatment for ischemic stroke and other diseases (such as hypertension, coronary heart disease, and diabetes), and physical therapy and occupational therapy for motor dysfunction will occur every day over 60 min (including preparation). Participants cannot receive antidepressant medication, or on any other acupuncture treatments that may affect the evaluation of the efficacy of the interventions of the study. The participants’ psychological condition will be closely monitored by a psychiatrist throughout the study period. Participants would be withdrawn from the study should any sign of deterioration in mental health condition and will be treated by a psychologist. The acupuncture group will receive acupuncture treatment, and the control group will receive sham acupuncture treatment. The participating physicians in the trial are acupuncture doctors at the Secondary Medical College of Guangzhou University of Traditional Chinese Medicine. As the acupuncturists are responsible for the acupuncture treatment, they are all highly qualified, have a master’s degree in acupuncture and moxibustion, have undergone training in a unified standardized operation plan. Acupuncture treatment will be administered in the supine position, and the temperature of the treatment room is maintained at 26 °C. Participants will receive 20 treatment sessions over a 4-week period at a frequency of 5 times per week.

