### Follow-up

To evaluate the persistence of the effects, a follow-up assessment will occur 1 month after the end of the 4-week treatment.

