### Outcome measures

The endpoints will be evaluated at baseline (before intervention), week 4 (immediately after intervention), and week 8 (1-month follow-up). We include two figures to show the participant timeline more clearly (see Figs. 1 and 2).

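### Adverse-event recording is stated only for the 4 treatment weeks, although follow-up runs to week 8, and nothing routes withdrawals for mental-health deterioration into the safety record

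*Protocol article*

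**What the plan says.** Safety is one of the trial's aims: the Introduction describes a study "designed to explore the efficacy and safety of acupuncture on PSD".

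The Safety evaluation section sets the recording window, "Adverse events (AEs) during the treatment will be recorded", and then gives examples: "AEs include the following: hematoma around the site of needling insertion points, local numbness, pain, and dizziness during treatment". The Intervention section fixes the length of treatment: "Participants will receive 20 treatment sessions over a 4-week period at a frequency of 5 times per week".

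Observation continues beyond that. Under Follow-up, "To evaluate the persistence of the effects, a follow-up assessment will occur 1 month after the end of the 4-week treatment", and under Outcome measures, "The endpoints will be evaluated at baseline (before intervention), week 4 (immediately after intervention), and week 8 (1-month follow-up"). The Data collection methods section makes the follow-up assessment a clinic visit.

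Other sections act on harms over a longer period. The Intervention section provides psychiatric monitoring for the whole study and states: "Participants would be withdrawn from the study should any sign of deterioration in mental health condition". The Termination criteria cover serious adverse reactions or aggravation at any time in the study. The Blinding section requires emergency unblinding for serious adverse reactions and gives no time limit.

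**The concern.** The window for recording adverse events is shorter than the window in which the plan itself expects to act on harms. Participants enter with a HAMD-17 score of at least 17 and take no antidepressants during the trial. Worsening mood is a harm that the plan foresees, since it is a reason for withdrawal. Yet it is not among the named adverse events, and no section links such a withdrawal to the adverse-event form.

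At stake is whether the safety comparison is complete. If the stated rule is followed literally, an event first arising after week 4 has no stated place in the adverse-event data. A participant withdrawn for deterioration may also leave no trace there, in either arm. These withdrawals bear on both safety and efficacy, so a comparison of arms that omits them is hard to interpret.

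**Working it through.** The plan gives no figure on this point to reproduce. The check sets the sections side by side and adds a small calculation of scale.

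**Step 1: windows**

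| Section | What it governs | Period |
|---|---|---|
| Safety evaluation | recording of adverse events | treatment (4 weeks) |
| Follow-up; Outcome measures | efficacy assessments | to week 8 |
| Intervention | psychiatric monitoring; withdrawal for deterioration | whole study for monitoring |
| Termination criteria | serious reactions or aggravation | whole study |
| Blinding | unblinding for serious reactions | no limit given |

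Share of the planned 8 weeks with stated recording: 4/8 = 50%. An event in weeks 4 to 8 that is serious enough to end participation falls under the Termination criteria but outside the stated recording window.

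**Step 2: could HAMD-17 show the worsening instead?** Three of the plan's rules combine here:

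- Endpoints are measured at baseline, week 4 and week 8 only (Outcome measures).
- Deteriorating participants are withdrawn (Intervention).
- Missing data are filled by last observation carried forward (Statistical analysis).

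No assessment at withdrawal is stated. If none is made:

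- Withdrawn before week 4: the imputed week-4 score is the baseline score, so change = baseline − baseline = 0.
- Withdrawn between weeks 4 and 8: the imputed week-8 score is the week-4 score, so any benefit at week 4 appears to persist.

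Worsening that leads to withdrawal could then be absent from the adverse-event table and also appear as no change, or as sustained benefit, in the efficacy data.

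**Step 3: scale, for illustration only.** The document gives no event rates. Assume an 8-week risk p between 1% and 10% and a constant hazard. The risk by week 4 is 1 − (1 − p)^(4/8), and the share of affected participants whose first event comes after week 4 is 1 − [1 − (1 − p)^(1/2)]/p.

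- p = 1%: 49.9% fall after week 4.
- p = 10%: 48.7% fall after week 4. With 28 per arm, 28 × 0.10 = 2.8 affected participants are expected over 8 weeks, about 1.4 of them by week 4.

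The trial is also small for safety. Zero events among 28 participants still allows a true risk of up to 1 − 0.05^(1/28) = 10.1% (one-sided 95% bound). With so few events expected, each unrecorded one matters. These figures show scale and do not decide the point.

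**The case against.** The strongest reply is that the article condenses a fuller protocol. The Safety evaluation section refers to the study protocol and to a form in the case report form, neither of which is shown. Definitions of adverse events, handling of serious events and collection during follow-up are often placed there. That stands as far as the types of event are concerned. It does not answer the window, which the article states.

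A reader might infer several stronger conclusions that the document does not support:

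- *That only needling effects and dizziness count as adverse events.* The list is introduced by *include* and is not closed. Mood worsening is not named, but it is not excluded.
- *That every event in weeks 4 to 8 is lost.* The Termination criteria and psychiatric monitoring run through the whole study, the Blinding section has no time limit, and the ethics committee supervises adverse reaction reports. None of these provisions stops at week 4. They do not, however, require recording as adverse events or tabulation by arm.
- *That deterioration goes unobserved.* It is monitored; what is missing is a stated link to the adverse-event record.
- *That deterioration is the only harm leading to withdrawal.* Serious adverse reactions are also a ground for termination.
- *That the data and safety monitoring committee would not see these events by arm.* The Data management section describes who sits on the committee, not what data it receives.

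It can also be said that HAMD-17 measures depression by arm at weeks 4 and 8 and that data from non-completers are to be included. For participants who stay in the trial that is a fair answer. For those withdrawn because of worsening it holds only if they are assessed at or after withdrawal, which is not stated.

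**Conclusion.** The point holds as a mismatch between sections. Recording of adverse events is stated for 4 of the 8 weeks of observation, while the plan acts on serious reactions, aggravation and deterioration beyond that window. No section sends withdrawals for deterioration to the adverse-event record. Because safety is a stated aim and a week-8 visit already exists, this should be corrected.

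The conclusion rests on reading *during the treatment* as the 4-week course. It also assumes that the unseen full protocol does not set a wider window. The efficacy consequence is conditional on no assessment being made at withdrawal. The number of events affected cannot be estimated from the document.

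**What to change.** Reconcile the Safety evaluation section with the Termination criteria, Intervention and Outcome measures sections:

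1. Record all untoward events, serious or not, in both arms from the first session to the week-8 visit. Keep the needling effects and dizziness as a solicited subset.
2. Count each withdrawal for deterioration or aggravation in the safety data, with its reason and date.
3. Tabulate adverse events and these withdrawals by arm.

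Timing limits what can still be collected prospectively. Recruitment was scheduled to end in December 2021 and the article appeared on 28 January 2022; someone enrolled on 31 December 2021 would reach week 8 on about 25 February 2022. For participants who have already finished, tabulate withdrawals and their reasons by arm from the study records, and state that this was done retrospectively.

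The cost is a few more adverse-event forms, a longer table and a wording change; the week-8 visit and psychiatric monitoring are already planned. Events already past may be only partly recoverable.

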#### Blinding

The acupuncturists are not blinded to group allocation. Participants are blinded to their group allocation but are informed that they had an equal chance of allocation to the acupuncture or control group before study participation. The outcome assessor will also be blinded to group allocation. Adverse reactions are carefully observed, and emergency unblinding is required if serious adverse reactions occur. Unblinding will be performed at the end of the trial to perform statistical analysis.

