#### Data management

The data and safety monitoring committee are composed of independent clinicians and biostatisticians with rich experience in clinical trials. The ethics committee of the Secondary Medical College of Guangzhou University of Traditional Chinese Medicine will perform random audits to ensure compliance with relevant regulations and guidelines. Any changes of the research protocol will be communicated to both the ethics committee and registration center timely. The case report form (CRF) is a paper version and should be properly recorded by the investigator. One researcher will be responsible for collecting data at each stage of the study, while another researcher will input the data into the SPSS software. This process will be carried out under the supervision of project monitors. According to the terms of informed consent, unless the subject’s consent is obtained, all the subject’s personal information is confidential and will not be disclosed to the public. The sponsor should keep CRF for 5 years after the end of the research.

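### On the natural reading, adverse events are judged and reported by unblinded acupuncture doctors, and no blinded assessor is named, so any between-arm safety report is open to observer bias

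*Protocol article*

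**What the plan says.** All references are to the protocol article.

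- **Aim.** The Introduction says the study was "designed to explore the efficacy and safety of acupuncture on PSD". The Abstract and Discussion also give safety as an aim.
- **Events.** Safety evaluation covers events during treatment and names "hematoma around the site of needling insertion points, local numbness, pain, and dizziness during treatment".
- **Who acts.** The same section says "If any AE occurs, the doctor will assess and provide corresponding treatment to the patient in accordance with the study protocol", and that this doctor will "report the adverse events form in the case report form". The doctor's role and blinding status are not given.
- **Who the doctors are.** Intervention says "The participating physicians in the trial are acupuncture doctors". It also gives a psychiatrist the task of following participants' psychological condition.
- **Blinding.** The Blinding section says "The acupuncturists are not blinded to group allocation". It blinds participants and the outcome assessor, and nobody else.
- **Technique.** Under Acupuncture group, needles are twirled until de qi is felt, a sensation that includes numbness. Under Control group, the sham needle does not penetrate the skin and is not manipulated.

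**The concern.** A safety comparison between randomized arms is fair only if an event has the same chance of being noticed, called adverse and written down in each arm. Here the person making those calls most plausibly knows the allocation and has just delivered the treatment. Pain, numbness and dizziness rest on what the participant reports and on how the recorder interprets it. A recorder who expects real needling to cause local effects may be readier to record them in that arm, or readier to pass over them as part of the treatment. Either way, a reader of the safety results could not separate the effect of acupuncture from the habits of the recorder.

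**Working it through.** This is a question of roles and definitions. It depends on no sample size, rate or error level, and the article gives no figure to reproduce, so the sections are set side by side.

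1. **Who assesses an event?** Safety evaluation says a doctor. Intervention says the participating physicians are acupuncture doctors. The only other medical role described in contact with participants is the psychiatrist, whose task is mental state, not needle-site or in-session events. The events listed are those that arise while an acupuncturist is treating. An acupuncture doctor is therefore the natural reading, though the article does not say so outright.

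2. **Is that person blinded?** Blinding says the acupuncturists are not. The two groups it does blind are participants and the outcome assessor. No section names a blinded assessor for adverse events.

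3. **Does judgement enter?** Of the four kinds of event listed, a hematoma can be seen. Local numbness, pain and dizziness are reported sensations that someone must decide to count.

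4. **Is the judgement the same in both arms?** Not for numbness. In the acupuncture arm it is one of the sensations the operator is told to produce; in the sham arm there is no manipulation and no such aim. Whether numbness is the intended response or an adverse event is thus a question that arises mainly in one arm, and it falls to someone who knows which arm it is.

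5. **Does any stated analysis depend on this?** Statistical analysis specifies no between-arm test of adverse events. The comparison follows from the safety aim and the sham-controlled design, so what is exposed is the by-arm safety report, not a named test.

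6. **Is it acknowledged?** The limitations in the Discussion mention that acupuncturists cannot be blinded, but draw from it only performance bias, not biased recording of adverse events.

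**The case against.** The strongest reply is that the doctor in Safety evaluation is not identified. Data management speaks of an investigator who completes the case report form and a researcher who collects data at each stage, so someone else might judge events. A condensed article may also leave the method of eliciting events to the full protocol. This stands in part: unblinded assessment is an inference, and the article's silence on a common prompt is no evidence that none exists. But the inference comes from what the article does state, and no section points to a blinded alternative.

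It can also be said that both arms have the same number of sessions, the same points and the same needle retention time, so the opportunity to observe is equal. That is correct. The concern is unequal judgement, not unequal observation.

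A reader might go further and infer that the adverse event record unblinds the HAMD-17 assessor: the form sits in the case report form, "The case report form (CRF) is a paper version and should be properly recorded by the investigator", and a hematoma at an insertion point suggests a penetrating needle. The documents do not support this as a finding. No section says that the assessor sees the adverse event pages or that these are filed with the outcome pages, and the assessor is stated to be blinded. The layout of the form and access to its pages are matters an article commonly leaves to the full protocol.

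**Conclusion.** The point holds as a cheap improvement of minor to moderate severity. On the natural reading of Safety evaluation, Intervention and Blinding together, adverse events are assessed and reported by unblinded acupuncture doctors, and no blinded assessor is named. Because safety is an aim, the events are partly subjective, and numbness is both a listed event and a sensation sought in the active arm only, a by-arm safety report is open to observer bias.

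The conclusion assumes that the unnamed doctor is one of the acupuncture doctors. If the full protocol assigns a blinded person, the point falls away. No size can be given: the documents contain no adverse event rates, and any figure would only restate an assumed rate and an assumed degree of under-recording. The direction is also open. An effect on the primary endpoint should not be inferred.

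**What to change.** Leave immediate care and the reporting of events with the treating doctor, as now. Take the between-arm comparison from a short fixed checklist that participants complete themselves, identical in both arms, for example weekly during the 4 weeks of treatment. It should cover the listed events and ask for sensations as felt, so that nobody who knows the arm decides whether numbness was intended. Results should be shown item by item, since numbness may be genuinely more common where it is sought. The checklist is only as masked as the participants are; the guess of treatment already planned after the last session in week 4 helps to judge that.

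When safety is reported, state who recorded adverse events and whether they knew the allocation. If treatment of all participants is already complete, this statement is the part that can still be made.

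As a precaution only, keep the adverse event form from the HAMD-17 assessor until each rating is signed.

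The cost is one self-completed page, some care in filing, and probably a few more minor events recorded in both arms.
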